**Conclusion:**

The results from this trial can guide future therapeutic protocols for NIBS treatments stimulating the PFC by demonstrating that the combination of NIBS techniques is feasible, tolerable, and can lead to greater enhancement of PFC activity.

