**Figure 1 f01:**
[figure not shown]
Protocol that will be applied. A) Sequence of the data acquisition and group allocation. B) Noninvasive brain stimulation protocol. atDCS = anodal transcranial direct current stimulation; AE = adverse effects; iTBS = intermittent Theta-burst stimulation; min = minutes; MRI = magnetic resonance imaging; SPECT = single photon emission computed tomography.

VAS and salivary cortisol will be collected immediately after the end of the session. For the VAS scale, participants will be asked to manually indicate on horizontal 10 cm lines whether they are experiencing any current pain. ‘Zero’ means ‘no pain’ and ‘ten’ means ‘pain as bad as it could possibly be’. To ensure the safety of both NIBS techniques alone and their combination, an Adverse Effects Scale^33^ will be assessed. This scale consists of identifying the produced effects and measuring them on a scale from 1 to 4 points, being 1 – absent, 2 – mild, 3 – moderate and 4 – severe. The working memory task (n-back) will be applied after measurement of adverse effects.

All of the procedures described above will take place at the Institute of Psychiatry - HCFMUSP. However, after the end of the working memory task, the volunteers will be taken to the Nuclear Medicine Center - HCFMUSP, where the SPECT images will be acquired by a trained team.

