### Statistical analyses

Sample size was calculated using G*Power 3.1 software.^38^ Since this is an original study and no a-priori power analysis is provided, we estimate a moderate *f* – size effect (0.25). The analysis considered four groups, 4 measurements, correlation between repeated measures of 0.5, alpha of 0.05 and power of 0.85, resulting in a sample size of 28 participants. Considering possible losses, we estimate recruitment of 30 subjects (120 observations).

The Shapiro-Wilk test will be applied to identify the sample distribution. Assuming a normal sample, we will perform analysis of variance (ANOVA) having ‘group’ as independent variable and ‘area of activation’ (observed in the left DLPFC) as dependent variable. The Kruskal-Wallis test will be performed in case of a non-parametric sample. The SPECT images will be available in orthogonal cuts in the transverse, sagittal, and coronal planes (DICOM format). Images will be analyzed using the Statistical Parametric Mapping software (SPM12; Wellcome Department of Imaging Neuroscience, London, UK), executed in Matlab Version 2020 (MathWorks, Natick, MA). We will use SPM to form a statistical map according to the statistical threshold to identify differences among the groups. In-house scripts will be used for partial volume correction procedures based on structural MRI. The SPM images will be subtracted from each group to verify areas of functional activation.

ANOVA or its non-parametric extension will be applied for n-back and salivary cortisol, with ‘group’ as independent variable for both outcomes and ‘cortisol level’ (for salivary cortisol) and accuracy/response time (for working memory performance) as ‘dependent variables’. The associations between n-back task performance (accuracy and response time)/salivary cortisol level and cerebral activation will be estimated with linear regression. We will perform pathway analyses to verify whether cerebral activation is directly associated with the results of working memory performance and cortisol salivary level or is measured by these findings. We will also statistically investigate the possible learning effects of the repetitive application of the working memory task by grouping participants’ scores according to the chronological order of NIBS intervention assignments.

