The mood scales administered before each NIBS session (such as HAMD, BDI, PANAS, and HAI) will be used to investigate major mood oscillation between sessions. If significant mood changes (p < 0.05) are found, we will use these measures as potential moderators of the main outcomes of this study. Moreover, the VAS will be used to investigate any significant change in pain intensity before and after each session as well as between NIBS sessions. Finally, ANOVA will also be applied to investigate adverse effects (dependent variable) across groups (independent variable).

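### The article foresees showing that combined stimulation is tolerable, but the only analysis it names for the adverse-effects scale is a difference test, which cannot show that with 30 participants

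*Protocol article*

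**What the plan says.** Three places in the protocol article bear on this.

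- **Procedure, text after Figure 1.** An Adverse Effects Scale is given after each session. Its purpose is stated: "To ensure the safety of both NIBS techniques alone and their combination". Each effect is identified and graded, "measuring them on a scale from 1 to 4 points", from absent through mild and moderate to severe.
- **Abstract, Conclusion.** The results are expected to guide later treatment protocols by "demonstrating that the combination of NIBS techniques is feasible, tolerable, and can lead to greater enhancement of PFC activity".
- **Statistical analyses, last paragraph.** The method for the scale is fixed in one sentence: "ANOVA will also be applied to investigate adverse effects (dependent variable) across groups (independent variable").

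The same paragraph says that pain on the visual analogue scale (VAS) will be examined for significant change before and after each session and between sessions. For the n-back task and cortisol the section names a non-parametric alternative to ANOVA. It names none for adverse effects. No expected rate, tolerability criterion or confidence interval is given for adverse effects. The planned size is 30 participants over four sessions: "we estimate recruitment of 30 subjects (120 observations").

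**The concern.** The named method does not fit the purpose stated for the scale. A comparison of mean scores asks whether the conditions differ. A statement that the combination is tolerable needs the opposite kind of evidence: how frequent moderate or severe effects are, and how large an excess over the other conditions the data can exclude. A p value gives neither, whether it is above or below 0.05.

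The mean score also loses what matters for safety. Among participants otherwise rated absent (score 1), one severe rating adds 4 − 1 = 3 points to the total, and three mild ratings add 3 × (2 − 1) = 3 points. The mean cannot tell them apart.

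At stake is the tolerability part of the abstract's conclusion, in a study that calls itself phase I and expects to inform treatment protocols.

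**Working it through.** **1. The plan's own figure.** Inputs from Statistical analyses: f = 0.25, 4 groups, 4 measurements, correlation 0.5, alpha 0.05, power 0.85. For a within-subject factor, λ = N·m·f²/(1 − ρ), with m − 1 and (N − k)(m − 1) degrees of freedom. With N = 28, m = 4 and k = 4, λ = 28 × 4 × 0.0625/0.5 = 14, on 3 and 72 degrees of freedom, and power is 0.878. The minimum is 27, which rounds up to 28 as a multiple of four. The stated 28 reproduces. The effect size behind it is generic and not tied to adverse effects.

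**2. How large a doubling is on the ANOVA scale.** The article gives no rates, so these are assumptions. Three conditions have absent/mild/moderate/severe at 60/30/8/2%, that is, 10% moderate or severe. The combined condition has 20%.

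- Base mean: 0.60 + 0.60 + 0.24 + 0.08 = 1.52.
- Base variance: (0.60 + 1.20 + 0.72 + 0.32) − 1.52² = 0.53, so the SD is 0.73.
- Combined mean if the extra cases come from absent (50/30/16/4%): 0.50 + 0.60 + 0.48 + 0.16 = 1.74.
- The SD of four means with one shifted by 0.22 is 0.22 × √3/4 = 0.095, so f ≈ 0.095/0.73 = 0.13.

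That is about half the planned 0.25. If the extra cases come from mild (60/20/16/4%), the combined mean is 1.64, the shift is 0.12 and f ≈ 0.052/0.73 = 0.07.

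**3. Power with 30 participants.** Simulation of one 1–4 score per session, generated from correlated normal variables cut at the percentages above, alpha 0.05, 3000 runs per cell. The article does not say whether the ANOVA will use the matching within participants, so both forms are shown.

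| Moderate or severe, 10% to 20% | Correlation 0 | 0.5 | 0.7 |
|---|---|---|---|
| Repeated-measures, extra from absent | 17.6% | 27.4% | 37.4% |
| Repeated-measures, extra from mild | 7.9% | 10.7% | 13.3% |
| One-way, extra from absent | 17.6% | 8.6% | 4.6% |
| One-way, extra from mild | 8.0% | 2.2% | 0.8% |

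Simulation error is up to about one percentage point, so the ends of these ranges can move by that much between runs.

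Other scenarios, over correlations 0 to 0.7:

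- 5% to 10%: repeated-measures 9–14%, one-way 1–9%.
- 20% to 40%: repeated-measures 47–90% (about 73% at correlation 0.5), one-way 35–48%.
- 10% to 30% (a tripling): about 6–92% over both tests and both sources of extra cases.

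With no true difference and correlation 0.5, repeated-measures ANOVA rejected in 4.4% of runs and one-way ANOVA in 0.7%.

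**4. What 30 participants can exclude.** This step needs no assumed rate. With 0 events in 30, the exact two-sided 95% upper bound is 1 − 0.025^(1/30) = 11.6%, and the one-sided bound is 1 − 0.05^(1/30) = 9.5%. With 3 events in 30 (10%), the exact 95% interval is 2% to 27%.

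**The case against.** The best defence is that the article is condensed. It says ANOVA will be used to investigate adverse effects, and nowhere that p > 0.05 will be read as tolerable. Counts by severity are routine in a safety table and may stand in a full protocol or analysis plan that is not shown. Pain on the VAS is a second tolerability measure. The stated outcomes are perfusion, n-back and cortisol, and tolerability appears only as one word in the abstract's conclusion.

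Much of this stands, and it rules out several stronger readings that a reader might infer:

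- **That the plan treats non-significance as proof of tolerability.** No sentence says so. It is an inference from joining the three places quoted.
- **That this ANOVA is the only safety analysis.** The VAS comparison is also planned, though it too is framed as a search for significant change.
- **That severe reactions will go unreported.** The article does not say that counts will be left out.
- **That tolerability is the trial's main product, or that this is the first combined study over the prefrontal cortex.** The outcomes listed in the abstract contradict the former. The Introduction, which cites one earlier combined trial there, contradicts the latter.
- **That ANOVA is invalid on a 1–4 scale.** The matched version held its type I error in simulation. The ordinal scale is a minor matter.
- **That power is poor in all circumstances.** It is fair for common effects or large increases when scores correlate strongly within a person.

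The defence does not remove the mismatch. The article does not leave the method open: it names one, and that method cannot deliver the conclusion foreseen. Matching raises power but does not turn a difference test into an estimate with a bound.

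**Conclusion.** The concern holds in a limited form: safety is the stated purpose of the scale and tolerability a foreseen conclusion, while the only analysis named for the scale is a test of equal mean scores.

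For a doubling from 10% to 20% in the combined condition, power is about 8–37% with repeated-measures ANOVA and about 1–18% with one-way ANOVA. These figures rest on an assumed base rate and severity split, latent correlations from 0 to 0.7, and extra cases drawn from either absent or mild. The upper bound of 11.6% after 0 of 30 events needs none of these assumptions. Nor does the main argument, which would hold even if power were high. The change should be made, but it does not put the trial's main outcomes in doubt.

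**What to change.** In Statistical analyses, replace the sentence on adverse effects with an estimation analysis:

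1. For each effect and condition, report the number and percentage of participants scoring 2 or more and scoring 3 or more, with exact 95% confidence intervals.
2. Report the paired difference in these percentages between the combined condition and each of the other three, with its 95% interval.
3. Keep a participant-matched test across conditions as support only.
4. State that any tolerability conclusion, including the one in the abstract, rests on the upper confidence limits and not on a non-significant test.

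The cost is a few sentences and one more table from data already being collected, with no change to design or sample size. The drawback is a less favourable-looking statement, because the intervals will show what 30 participants cannot exclude.

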## Discussion

This study will be a phase-I trial designed to assess the combined and standalone effects of the tDCS and iTBS interventions over the PFC using multimodal assessments, comprising neuroimaging, cognitive tests, and salivary cortisol measures, which will be essential to evaluate the effects of concomitant NIBS administration, as well as to enhance knowledge regarding the effects of individual application of the techniques.

Considering the previous studies investigating the effects of two NIBS interventions^20 , 21 , 39^ and neuroimaging studies evaluating the online effects of tDCS over the DLPFC (17 subjects for two groups, with a total of 34 observations),^40^ our study presents the largest sample recruited to date. Besides, the within-subject full-factorial design will allow us to analyze a total of 120 observations. This sample decreases the chances of type I and type II errors, compared to previous studies.

Regarding the combined protocol adopted in our study, although application of dual facilitatory protocol stimulation can increase the chance of provoking homeostatic plasticity effects,^21^ this approach was chosen since previous studies have shown that induction of both LTP (long-term potentiation) or LTD (long-term depression) by burst stimulation depends on the membrane potential of the postsynaptic neurons and that the effects of stimulation can be modified by external hyper/depolarization.^20 , 41^ Besides, according to the literature, tDCS effects are improved by a concept known as ‘functional targeting,’^17^ in which neuronal networks that are already activated might be more stimulated compared to non-primed ones. Following these findings, the rationale behind the concurrent application of tDCS and iTBS is that DC current will probably bias iTBS effects.^20^ Moreover, it is important to underscore that the protocol for this study is slightly different from the ‘priming’ protocols of the previous studies with TMS,^42^ since here the stimulation protocols will be applied concomitantly and both NIBS protocols are associated with neuronal facilitation.

Along these lines, 99mTc-ECD SPECT was the imaging methodology of choice since it can measure direct and online brain perfusion of the NIBS protocols and the 99mTc-ECD radiopharmaceutical has low intrasubject variability.^43^ Thus, we decided to perform SPECT instead of other neuroimaging methods because 1) SPECT is a well-known method; 2) compared with the Positron Emission Tomography technique, SPECT uses longer-lived, more easily obtained radioisotopes, allowing us to apply the cognition task before acquisition of neuroimaging^44^ ; 3) combining two NIBS techniques and MRI simultaneously is extremely challenging; and 4) SPECT provides a direct measure of cerebral perfusion, in contrast to the fMRI technique, which is based on the BOLD signal and has low test-retest reliability at rest for tDCS studies.^45^ In fact, brain perfusion SPECT has already been applied to investigate the acute effects on regional cerebral blood flow (rCBF) of low-frequency (LF) and HF-rTMS in depressed patients,^46^ as well as to evaluate the effects of rTMS and antidepressant drugs in patients with Parkinson disease and depression^47^ pre/post treatments. Both studies showed directional, significant regional cerebral blood flow (rCBF) alterations after NIBS intervention over the PFC.

Moreover, the other assessments (working memory performance and salivary cortisol) will expand the findings of this study. The PFC and its neural network are associated with several cognitive functions^6^ and play an important role in emotional responses, processing and regulating stress.^48^ For instance, the DLPFC shows activation when sadness is suppressed voluntarily^49^ and co-activation with the amygdala during emotion reappraisal.^50^ In stressful events, the amygdala may activate other brain regions and, respectively, increase cortisol levels. Studies have already shown that a single session of tDCS over the DLPFC can change cortisol levels during negative visual stimuli.^48 , 51^ Analyzing cortisol measures in our study will allow us to identify if the iTBS and tDCS protocols (as monotherapy or combined) play an important role in changes to cortisol levels compared to sham protocol, as well as to compare these measures to brain activity in the different protocols. The same will be conducted using the working memory performance measure. In fact, instead of other cognitive domains such as attention, executive functions, or social cognition that are also related to the PFC function, working memory was chosen as the cognitive outcome of this study because this domain is the most investigated in NIBS trials to date^52^ and because previous trials have also shown that working memory is a potential marker for depression.^36^ Moreover, acquisition of SPECT neuroimaging within one hour of radiotracer injection makes it difficult to investigate any other measures.

Finally, the effects of the combination of tDCS and rTMS protocols have already been investigated for patients with stroke and tinnitus, for instance. In general, the results of the combined protocol showed significant clinical improvement when compared to the interventions as monotherapy.^53 , 54^ Accordingly, demonstrating the combined effects of two NIBS interventions over the PFC is important for further directions for therapeutic protocols given that both tDCS and iTBS techniques are limited as monotherapies for the treatment of PFC dysfunctions. For instance, standard rTMS protocols show a response rate of only 35% for depressed patients.^55^ Although the iTBS protocol is a recent U.S. Food and Drug Administration (FDA) approved technique for depression,^30^ meta-analyses indicate that its response rate is similar to standard rTMS protocols.^10 , 11^ Likewise, tDCS trials are still reporting heterogeneous results.^14 , 56 , 57^

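### A within-subjects trial sized as repeated measures is to be analysed with an ANOVA on group and Kruskal-Wallis; as written this drops the pairing and cuts power from about 0.90 to about 0.55

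*Protocol article*

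**What the plan says.** The Design section describes a within-subjects, full-factorial study, and the abstract has every volunteer attend four sessions, one per combination of active and sham tDCS and iTBS.

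The sample size in Statistical analyses is a repeated-measures calculation: "The analysis considered four groups, 4 measurements", with a "correlation between repeated measures of 0.5", "alpha of 0.05 and power of 0.85", an f of 0.25, and "resulting in a sample size of 28 participants". The text continues: "Considering possible losses, we estimate recruitment of 30 subjects (120 observations").

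The same section then sets the analysis. It is an ANOVA with group as the independent variable and activation in the left DLPFC as the dependent variable, with Kruskal-Wallis if the data are not normal. The n-back and cortisol outcomes get the ANOVA on group or its non-parametric extension. For the images, "The SPM images will be subtracted from each group to verify areas of functional activation". No participant or repeated-measures term is named for any outcome.

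The Discussion states that "the within-subject full-factorial design will allow us to analyze a total of 120 observations" and goes on to claim fewer type I and type II errors than earlier studies, having cited one imaging study with 34 observations.

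**The concern.** In a crossover, the gain in precision comes from comparing each person with himself or herself. The sample size uses that gain through the correlation of 0.5. An ANOVA with only a group factor leaves stable differences between people in the error term, and Kruskal-Wallis ranks all observations as if they came from separate people. The conditions are then tested against an error that is too large. A real effect of the size planned for would be missed far more often than the stated power suggests.

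The unpaired form also has a weakness when data are incomplete. Someone who misses one session contributes to three condition means and not to the fourth, so the means are no longer taken over the same people. A within-participant contrast does not have this problem.

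Finally, the plan expects losses, yet its Discussion argues from the count that would arise with none.

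**Working it through.** **Inputs.** From Statistical analyses: f = 0.25, m = 4 measurements, k = 4 groups, correlation ρ = 0.5, α = 0.05, target power 0.85, calculated N = 28, recruited N = 30. Assumed: within-condition SD of 1, equal correlations and sphericity.

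**1. The plan's own figure.** For a within-factor repeated-measures ANOVA, λ = f²·N·m/(1−ρ), df1 = m−1 and df2 = (N−k)(m−1).
- At N = 28: λ = 0.0625 × 28 × 4 / 0.5 = 14, df = 3 and 72, power 0.878.
- The smallest N reaching 0.85 is 27, rounded up to 28 as a multiple of 4. So 28 reproduces.
- Treated as one group (k = 1), the smallest N is 26 (power 0.851); power is 0.880 at 28 and 0.904 at 30.
- The between-factor version would need 128 and the within-between interaction 40. Only the within-factor calculation gives 28, so the sample size presupposes a paired analysis.

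**2. The stated analysis on the same data.** Take 30 complete participants and 120 observations.
- Condition sum of squares: (1−ρ) = 0.5 times a chi-square on 3 df with noncentrality 0.0625 × 30 × 4 / 0.5 = 15.
- Error in an ANOVA on group alone (116 df) pools two parts. Between participants it is (1 + 3ρ) = 2.5 times a chi-square on 29 df. The residual is 0.5 times a chi-square on 87 df.
- Expected error mean square: (2.5 × 29 + 0.5 × 87)/116 = (72.5 + 43.5)/116 = 1.0. The paired analysis uses the residual alone, 0.5, so the stated test divides by an error twice too large.

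Simulated results:

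| Analysis, 30 complete participants | Power | Type I error |
|---|---|---|
| ANOVA on group only | about 0.55 | about 0.002 to 0.003 |
| Paired (participant in the model) | about 0.90 | 0.05 |

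As a cross-check, a one-way ANOVA at f = 0.25 on truly independent observations (λ = f² × number of observations) has power 0.61 with 120 (λ = 7.5) and 0.57 with 112 (λ = 7.0). Losing eight observations matters much less than losing the pairing.

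**3. Missed sessions.** In a simulation of 30 people with no true difference, one condition was missed by some participants (rates assumed). The contrast compares it with a condition that everyone completed.

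| Missingness | Unpaired bias | Paired bias |
|---|---|---|
| Unrelated to outcome, 6.7% or 10% | about 0.00 SD | about 0.00 SD |
| Only people with below-average levels, 6.7% | about 0.04 SD | about 0.00 SD |
| Only people with below-average levels, 10% | about 0.06 SD | about 0.00 SD |

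The standard error of the contrast is about 0.19 SD. A harsher illustration: if 3 of 30 miss one condition and average 1 SD below the other 27, the mean of those 27 exceeds the full mean by 3/30 = 0.10 SD. If only one condition differs, f = 0.25 corresponds to 0.25/√(3/16) = 0.577 SD, so the shift is 0.10/0.577 = 17% of the planned effect.

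**4. The count.** 30 × 4 = 120 with no loss. 28 × 4 = 112 if two participants are lost, which is 2/30 = 6.7%.

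**The case against.** The strongest reply is that the article condenses a fuller plan. The design is called within-subjects, the sample size uses a repeated-measures correlation, and the n-back section says order will enter the models. A reader could take ANOVA to mean repeated-measures ANOVA, with the participant term left to the SAP. For the word ANOVA alone this has force. It does not cover Kruskal-Wallis, which is an independent-samples test chosen by name. With group as the only stated factor, the text fixes an unpaired analysis and does not merely leave one open. The image-subtraction sentence is ambiguous: it does not say whether subtraction is within a person or between condition averages, so it needs clarifying and is not shown to be wrong.

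Three stronger readings are tempting, and the document does not support them.
- *The 120 is an error that undermines the trial.* It is the correct product for 30 recruits, the Statistical analyses section attaches it to recruitment, and the Discussion wording can be read as a ceiling. No power figure is computed from it, and against 34 observations the choice between 112 and 120 changes nothing.
- *Incomplete participants bias the contrasts.* Bias needs both an unpaired analysis and missingness tied to outcome level. Order is randomised and counter-balanced, so ordinary dropout should spread over the conditions.
- *The plan lacks a rule for missed sessions, or its loss allowance is too small.* Such a rule is commonly held in the full protocol or SAP. On the one-group calculation the 0.85 target still holds at 26 completers.

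**Conclusion.** The concern holds for the mismatch between design and analysis. On the plan's own inputs, the analysis as written has power of about 0.55 where the paired analysis has about 0.90, and it rejects a true null about 0.2% to 0.3% of the time instead of 5%. The error is towards missed effects, not false positives. These figures rest on a correlation of 0.5, sphericity, 30 complete participants and the literal reading of the text; if a repeated-measures ANOVA was meant, the loss of power applies only to the Kruskal-Wallis fallback and to any unpaired image comparison.

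Bias from missed sessions is a conditional, secondary point: none if missingness is unrelated to outcome, and 0.04 to 0.06 SD in the selective simulation under assumed rates. The 120 count is a small matter of wording. The sample size of 28 reproduces and is not in question.

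**What to change.** In Statistical analyses, state that condition effects are estimated within participant:
- a mixed model with a participant effect, using all completed sessions, for left DLPFC activation, n-back accuracy and response time, and cortisol;
- a subject factor in the SPM model, with images subtracted only within the same participant;
- a paired rank test in place of Kruskal-Wallis, such as Friedman's test for participants with complete data.

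In the Discussion, give the count as up to 120 observations, or 112 if the two allowed losses occur.

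The cost is wording and model specification. No further participants, visits or scans are needed, the sample size stands, and the only concession is a slightly less favourable observation count.
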